**2.4 treatment protocol**

Participants will be randomly assigned in a 1:1 ratio to either the electroacupuncture (EA) group or the sham acupuncture (SA) group. Acupuncture interventions will be administered by licensed Traditional Chinese Medicine (TCM) acupuncturists at each study center. All practitioners are required to hold a valid TCM physician license issued by the People’s Republic of China and possess at least three years of clinical experience.

A standardized acupuncture protocol will be employed in the EA group, with two alternating sets of primary acupoints:

Set 1: Zhongliao (BL33), Ciliao (BL32), Sanyinjiao (SP6), and Taixi (KI3)

Set 2: Tianshu (ST25), Shuidao (ST28), Zusanli (ST36), and Yinlingquan (SP9)

Only one set of acupoints will be used per treatment session, with the two sets alternated throughout the intervention period. Detailed acupoint locations are provided in Table 1.

Sterile, single-use Hwato-brand acupuncture needles (0.40 mm × 30 mm or 0.25 mm × 30 mm) will be used for all procedures. Prior to needling, both the acupoint sites and the practitioner’s hands will be disinfected thoroughly with 75% alcohol. Manual needle insertion will follow the balanced reinforcing-reducing technique through bidirectional rotation for 30 seconds to elicit the “deqi” sensation. After achieving deqi:

In Set 1, electroacupuncture stimulation will be applied to bilateral BL32 and paired between SP6 and KI3.

In Set 2, stimulation will be applied to bilateral ST25 and paired between ST36.

The intensity of electrical stimulation will be adjusted to the maximum tolerable level that produces slight tremor at the needle handle. A continuous wave at 10 Hz will be used, and all needles will be retained in situ for 30 minutes.

**Table 1. Location of acupoints in EA group.**

| **Acupoints** | **Locations** |
| --- | --- |
| Zhongliao (BL33) | In the sacral region, opposite the third sacral posterior foramen |
| Ciliao (BL32) | In the sacral region, the second sacral posterior foramen |
| Sanyinjiao (SP6) | On the medial of the lower leg, 3 cun^a^ above the tip of the medial malleolus, posterior to the medial margin of the tibia |
| Taixi (KI3) | On the medial side of the foot, in the depression between the medial tip of the ankle and the Achilles tendon |
| Tianshu (ST25) | On the abdomen, level with the umbilicus, 2 cun lateral to the anterior midline |
| Shuidao (ST28) | On the abdomen, 3 cun below the umbilicus, 2 cun lateral to the anterior midline |
| Zusanli (ST36) | On the anterolateral side of the lower leg, 3 cun below the Dubi (ST35) point, one finger-width (middle finger) lateral to the anterior crest of the tibia |
| Yinlingquan (SP9) | On the medial side of the lower leg, in the depression between the inferior border of the medial condyle of the tibia and the medial border of the tibia |

^a^1 cun (≈20 mm) is defined as the width of the interphalangeal joint of patient’s thumb

Participants in the sham acupuncture group will receive superficial needling without manual stimulation and without the elicitation of the deqi sensation. Two sets of non-acupoints (Non-acupoints 1–4 and Non-acupoints 5–8) will be used alternately in each session. Sham electroacupuncture will be applied by attaching electrodes to bilateral Non-acupoint 4 and Non-acupoint 8.Although the electrode wires will be connected to the electroacupuncture device, no electrical current will be delivered. Specifically, the red wires used for stimulation will be disconnected internally to ensure no active current passes through. All needles will remain in place for 30 minutes.

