**2.3 Randomization and Blinding Procedures**

A stratified block randomization method will be employed, with stratification based on study centers. Eligible participants will be randomly assigned in a 1:1 ratio to either the electroacupuncture (EA) group or the sham acupuncture (SA) group. The randomization sequence will be generated using SAS software by an independent statistician who is not involved in any aspect of the trial. Randomization numbers will be managed and safeguarded by a designated randomization coordinator, who will not participate in the intervention, outcome assessment, or statistical analysis.

For each eligible participant enrolled, the screening personnel will obtain the corresponding randomization number by phone from the randomization coordinator. Throughout the trial, the randomization sequence will remain concealed from all other study personnel to ensure allocation concealment.

Blinding will not be applied to the acupuncturists due to the nature of the intervention. However, patients, outcome assessors, and statistical analysts will remain blinded to group allocation to minimize potential bias.

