**Table 2. Location of acupoints in SA group.**

| **Acupoints** | **Locations** |
| --- | --- |
| non-acupoint 1 | In the sacral region, 1 cun^a^ lateral to the Zhongliao (BL33) point |
| non-acupoint 2 | In the sacral region, 1 cun lateral to the Ciliao (BL32) point |
| non-acupoint 3 | On the lower limb, 2 cun above the medial malleolus, the medial side of the tibia is median, between the Liver and Spleen meridians |
| non-acupoint 4 | On the lower limb, at the midpoint of the line connecting Qiuxu (GB40) and Jiexi (ST41) points |
| non-acupoint 5 | On the abdomen, 2 cun below the umbilicus and 1 cun apart from the midline |
| non-acupoint 6 | On the abdomen, 2 cun above the anterior superior iliac spine |
| non-acupoint 7 | On the lower limb, on the lateral side of the lower leg, 3 cun below the Yanglingquan (GB34) point, between the Gallbladder and Bladder meridians |
| non-acupoint 8 | On the lower limb, on the medial side of the lower leg, 1 cun lateral to the Chengjin (BL56) point, between the Bladder and Stomach meridians |

^a^1 cun (≈20 mm) is defined as the width of the interphalangeal joint of patient’s thumb

Participants in both groups will receive acupuncture three times per week during the first four weeks (Weeks 1–4), and twice per week during the subsequent four weeks (Weeks 5–8), for a total of 20 sessions over an 8-week treatment period. No additional therapies targeting low anterior resection syndrome (LARS) will be permitted during the study period.

In cases of severe fecal incontinence, participants may be allowed to take loperamide hydrochloride capsules (Imodium) as needed for symptom relief.

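### Sham leads are fixed on two lower-limb needles only, while every active session also wires the sacrum or abdomen: an avoidable cue that can weaken patient blinding

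*Protocol*

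**What the plan says.** Section 2.3 leaves the acupuncturists unblinded and then states: "However, patients, outcome assessors, and statistical analysts will remain blinded to group allocation to minimize potential bias".

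Section 2.4 fixes the active leads. For the first set: "In Set 1, electroacupuncture stimulation will be applied to bilateral BL32 and paired between SP6 and KI3". For the second: "In Set 2, stimulation will be applied to bilateral ST25 and paired between ST36". Only one set is used per session. On the current it says: "The intensity of electrical stimulation will be adjusted to the maximum tolerable level that produces slight tremor at the needle handle".

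The sham text, below Table 1 in the same section, alternates in the same way: "Two sets of non-acupoints (Non-acupoints 1–4 and Non-acupoints 5–8) will be used alternately in each session". The leads are placed as follows: "Sham electroacupuncture will be applied by attaching electrodes to bilateral Non-acupoint 4 and Non-acupoint 8". They are inert: "Although the electrode wires will be connected to the electroacupuncture device, no electrical current will be delivered". The text adds that the stimulating wires are disconnected internally. Sham needling is superficial and does not seek deqi.

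Table 2 puts both wired sham points on the lower limb. Non-acupoint 4 is located "On the lower limb, at the midpoint of the line connecting Qiuxu (GB40) and Jiexi (ST41) points", and non-acupoint 8 is on the lower leg. Non-acupoints 1 and 2 are sacral, and 5 and 6 are abdominal. All four are needled, but none carries a lead.

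Section 2.5 makes the primary outcome the change in LARS score at week 8 and describes the score as self-rated. The same section places the credibility, expectancy and blinding assessments after the first treatment session.

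**The concern.** Dummy leads have one purpose: to make the sham look like electroacupuncture to the patient. This sham copies the active arm in needle regions, alternation of sets, retention time and number of sessions. It departs from it in how many needles are wired and in whether the trunk is wired at all.

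Blinded assessors cannot protect an outcome that patients rate themselves, so the primary comparison depends on patient blinding. A patient who knows that electroacupuncture for this condition would put leads on the sacrum or abdomen, and sees leads only on the leg, has a clue to the allocation. If that shifts expectation differently in the two arms, part of the week-8 difference could reflect expectation. The planned difference is small, 6.8 − 4.1 = 2.7 points (section 2.2), so patient blinding deserves every inexpensive support.

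**Working it through.** **Inputs.** Active lead sites: section 2.4. Sham lead sites and alternation: text below Table 1. Body regions: Tables 1 and 2. Schedule: text below Table 2.

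**Sessions.** 3 per week × 4 weeks + 2 per week × 4 weeks = 12 + 8 = 20, which reproduces the plan's stated total.

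**Wired needles per session.** Count = trunk needles + lower-limb needles carrying a lead.

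- Active Set 1: bilateral BL32 gives 2. The SP6–KI3 pair gives 2 if wired on one leg and 4 if on both; the protocol does not say which. Total 2 + 2 = 4 to 2 + 4 = 6.
- Active Set 2: bilateral ST25 gives 2. The ST36 pairing names no partner. Read as left with right it gives 2; read as a single wired needle it gives 1. Total 2 + 1 = 3 to 2 + 2 = 4.
- Sham, either set: non-acupoint 4 belongs to the set 1–4 and non-acupoint 8 to the set 5–8, so only one of them is in use in any session. Bilateral placement gives 2.

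| | Active | Sham |
|---|---|---|
| Wired needles, Set 1 | 4 to 6 | 2 |
| Wired needles, Set 2 | 3 to 4 | 2 |
| Of these, on the trunk | 2 (sacrum or abdomen) | 0 |
| Sessions with trunk leads | 20 of 20 | 0 of 20 |

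The active arm has more wired needles on every reading: 2 to 4 more in Set 1 and 1 to 2 more in Set 2. The trunk contrast does not depend on the open laterality, because BL32 and ST25 are both stated to be bilateral. Both arms have leads on the lower limb, so the regional difference is the absence of sacral and abdominal leads in the sham and nothing wider.

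**Is the difference needed to keep the sham inert?** No. The leads carry no current because of the internal disconnection, wherever they are clipped.

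**Size of bias.** The documents give neither the share of patients who might infer their arm from the leads nor the effect of such knowledge on the LARS score. No estimate can be derived. The sample size of 136 does not depend on this point.

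**The case against.** The strongest reply is that this is a parallel-group trial and each patient sees only one set-up. Leads on the leg alone reveal nothing to someone who does not know what the other arm looks like, and the protocol describes no shared treatment rooms or contact between patients. This stands, and it limits the cue mainly to patients with earlier acupuncture experience (section 2.1.4 excludes only treatment within the past month) and to those who hear about the other set-up. A reader might infer that lead placement will unblind the trial; the documents do not support that.

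Second, absent current and absent deqi are stronger cues, and matching the leads leaves them in place. This also stands. Those cues belong to the sham that was chosen, whereas the lead mismatch does not and can be removed.

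Third, a reader might infer that the sham omits any intensity-setting step. The protocol is only silent here. Section 2.10 provides for SOPs covering all stages and for central training, and a dummy device routine could sit there. It is therefore a secondary point and not a stated error. Asking a sham patient about tolerance could also draw attention to the missing sensation. An SOP would not settle the lead sites, which the protocol fixes itself.

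Fourth, section 2.5 plans credibility, expectancy and blinding assessments. These could show an early difference between arms. They come after session 1 of 20, when the patient has met only one of the two alternating set-ups, and they do not cover week 8.

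**Conclusion.** The point holds as a cheap improvement to the sham design. By the protocol's own text, every active session wires two trunk needles plus the lower limb (4 to 6 needles in Set 1, 3 to 4 in Set 2), and every sham session wires two lower-limb needles only. The direction is the same on every reading of the unstated laterality. The mismatch serves no purpose in keeping the sham inert, and it can weaken the patient blinding claimed in section 2.3 for a self-rated primary outcome.

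It is tempting to attach a number of LARS points to this and set it against the planned 2.7. Nothing in the documents anchors such a figure or separates the effect of the leads from that of the missing current, so the size of any bias remains unknown.

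**What to change.** Reconcile the sham text below Table 1 with the active lead description in section 2.4 and the blinding statement in section 2.3. Attach the internally disconnected leads to the same number of sham needles, in the same regions, as in the matching active set: sacral plus lower limb when non-acupoints 1–4 are used, abdominal plus lower limb when 5–8 are used. To make the match exact, the protocol should first state which needles carry leads in each active set (the legs for SP6–KI3, the partner for ST36) and whether the sacral and abdominal sham needles are placed on both sides.

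The cost is protocol and SOP wording, a few more dummy clips per session and a slightly longer sham set-up. No current is added, and active treatment and sample size are unchanged. The change reduces one cue and leaves those from absent current and deqi. As a secondary matter, the sponsor can confirm whether an SOP covers a dummy device-setting routine, bearing in mind that its wording could itself point to the missing sensation.

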**Table 2. Location of acupoints in SA group.**

| **Acupoints** | **Locations** |
| --- | --- |
| non-acupoint 1 | In the sacral region, 1 cun^a^ lateral to the Zhongliao (BL33) point |
| non-acupoint 2 | In the sacral region, 1 cun lateral to the Ciliao (BL32) point |
| non-acupoint 3 | On the lower limb, 2 cun above the medial malleolus, the medial side of the tibia is median, between the Liver and Spleen meridians |
| non-acupoint 4 | On the lower limb, at the midpoint of the line connecting Qiuxu (GB40) and Jiexi (ST41) points |
| non-acupoint 5 | On the abdomen, 2 cun below the umbilicus and 1 cun apart from the midline |
| non-acupoint 6 | On the abdomen, 2 cun above the anterior superior iliac spine |
| non-acupoint 7 | On the lower limb, on the lateral side of the lower leg, 3 cun below the Yanglingquan (GB34) point, between the Gallbladder and Bladder meridians |
| non-acupoint 8 | On the lower limb, on the medial side of the lower leg, 1 cun lateral to the Chengjin (BL56) point, between the Bladder and Stomach meridians |

^a^1 cun (≈20 mm) is defined as the width of the interphalangeal joint of patient’s thumb

Participants in both groups will receive acupuncture three times per week during the first four weeks (Weeks 1–4), and twice per week during the subsequent four weeks (Weeks 5–8), for a total of 20 sessions over an 8-week treatment period. No additional therapies targeting low anterior resection syndrome (LARS) will be permitted during the study period.

In cases of severe fecal incontinence, participants may be allowed to take loperamide hydrochloride capsules (Imodium) as needed for symptom relief.

**Combined Medication Regulations:**

The related medication was recorded

**2.5 Outcome Measures**

**Primary outcome**

Change in LARS score from baseline at week 8.

The LARS score is a validated self-rating scale to assess bowel function after low rectal resection and consists of five items: fecal incontinence, urinary incontinence, bowel frequency, bowel aggregation, and urgency, with scores ranging from 0 to 42. The severity of bowel dysfunction can be categorized as: no LARS (0-20), mild LARS (21-29), or severe LARS (30-42).

**Secondary outcome**

① Changes in LARS Score from Baseline at Week 2, 4, 6, 12 and 24.

② Proportion of Patients with Improvement in Bowel Dysfunction

At weeks 2, 4, 6, 8, 12, and 24, the number of patients improving from severe LARS to mild LARS, from mild LARS to no LARS and from severe LARS to no LARS will be determined according to LARS score.

③ Subjective distress of intestinal symptoms

We will assess subjective distress of intestinal symptoms by the Numerical Rating Scale (NRS) at Week 4, 8, 12 and 24, where 0 indicates no distress, and 10 represents the worst imaginable distress.

④ EORTC-QLQ-C30 Quality of Life Questionnaire

The core quality of life questionnaire developed by the European Organization for Research and Treatment of Cancer (EORTC-QLQ-C30), comprising 30 items. It includes 5 functions, 3 symptoms, 1 global health status, and 6 single-item measures. Higher scores on the functional scales indicate better quality of life, whereas higher scores on the symptom scales indicate worse quality of life. Patients were evaluated at weeks 4, 8, 12, and 24.

⑤ Bristol Stool Diary

During the week 0, 4, 8, 12 and 24, we will record bowel movement frequency, stool consistency and urgency over the past week.

⑥ Fecal Incontinence Quality of Life Scale (FIQL)

We will evaluate the quality of life in patients with fecal incontinence, covering four aspects: lifestyle changes, coping/behavior limitations, depression/self-perception, and social embarrassment at week 0, 4, 8, 12 and 24.

⑦ Diarrhea Wexner Score:

we will evaluate at week 0, 4, 8, 12 and 24.

⑧ Credibility and Expectancy Assessment:

The credibility of the intervention and participants’ treatment expectations will be evaluated immediately following the first treatment session.

⑨ Blinding Assessment:

Blinding effectiveness will also be assessed at the end of the first treatment session.

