2.1.3 Inclusion criteria

① Age between 18 and 75 years of any gender;

② Diagnosis of LARS confirmed at least one month after rectal resection or stoma closure (LARS score ≥ 21).

③ Provide written informed consent.

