**2.2 Sample size**

Based on previous study, we speculated that the LARS score would be decreased by 6.8 points in the electroacupuncture group and 4.1 points in the sham-electroacupuncture group, with a standard deviation of 5. Considering a 20% dropout rate, it is estimated that a total of 136 subjects will need to be recruited.

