**2.8 Data Entry and Statistical Analysis**

A modified intention-to-treat (mITT) approach will be applied. All randomized participants who meet inclusion criteria will be included in the statistical analysis. Continuous variables will be expressed as mean ± standard deviation (M ± SD) or as median with interquartile range, depending on distribution. Categorical variables will be presented as frequencies, proportions, or percentages.

Baseline demographic and clinical characteristics will be compared using analysis of variance (ANOVA) or chi-square (χ²) tests. Between-group differences in outcomes will be analyzed using t-tests, rank-sum tests, ANOVA, or χ² tests, as appropriate. For repeated measures outcomes, repeated-measures ANOVA will be employed.

All statistical tests will be two-sided, with a significance level of α = 0.05. A p-value < 0.05 will be considered statistically significant. Statistical analyses will be conducted using SPSS software.

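### Secondary outcome 2 should be one LARS-category endpoint adjusted for baseline LARS score, not three shift counts compared with unadjusted tests

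*Protocol*

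**What the plan says.** Protocol section 2.5, secondary outcome 2, carries the heading "Proportion of Patients with Improvement in Bowel Dysfunction". The text beneath it determines "the number of patients improving from severe LARS to mild LARS, from mild LARS to no LARS and from severe LARS to no LARS" and does so "At weeks 2, 4, 6, 8, 12, and 24". It does not say whether the three shifts are added together or compared one by one, and it gives no denominator.

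The bands come from the primary-outcome text: "no LARS (0-20), mild LARS (21-29), or severe LARS (30-42". Section 2.1.3 admits patients with "LARS score ≥ 21", so everyone starts mild or severe.

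For the analysis, section 2.8 says: "Between-group differences in outcomes will be analyzed using t-tests, rank-sum tests, ANOVA, or χ² tests, as appropriate". It assigns no test to this outcome and names no model with a baseline covariate. Section 2.3 stratifies randomisation by study centre only.

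The primary outcome is "Change in LARS score from baseline at week 8". Secondary outcome 1 is the same change at weeks 2, 4, 6, 12 and 24.

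**The concern.** Three features combine badly.

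- **Baseline dependence.** Whether a patient can cross a band edge depends mostly on how far from it the patient starts. An unadjusted test treats this large, known source of variation as noise, and severity is not a stratum that would balance it.
- **Non-monotone count.** Severe-to-mild and severe-to-none exclude each other. If severe-to-mild is tested alone, a patient who does better still leaves that count. Mild-to-none does not compete with these two, because it draws on a different baseline group.
- **Open choice.** Three shifts at six visits give 3 × 6 = 18 possible comparisons, against 6 for a single endpoint. The text does not say which is meant.

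At stake are the power and readability of a secondary outcome, and the room to pick the most favourable shift after the results are known.

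**Working it through.** **Inputs.** Section 2.2: scores "decreased by 6.8 points in the electroacupuncture group and 4.1 points in the sham-electroacupuncture group", SD 5, 20% dropout, total 136. Section 2.5: bands 0–20, 21–29, 30–42. Section 2.8: two-sided α = 0.05. Assumed, because the protocol does not give them: 80% power, normally distributed change, all whole-number scores attainable, and the baseline distribution.

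**1. The plan's own figure.** n per arm = 2 × (1.960 + 0.842)² × 5² / 2.7² = 53.8, so 54. Then 54 / 0.8 = 67.5, so 68 per arm and 136 in total. This reproduces the protocol and gives 54 analysed per arm.

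**2. Probability of each shift by baseline score b, with mean fall m.**
P(no LARS) = Φ((20.5 − b + m)/5). P(not severe) = Φ((29.5 − b + m)/5). P(severe to mild) is the second minus the first.

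Example, b = 30:
- Electroacupuncture (EA), m = 6.8: Φ(−0.54) = 0.295; Φ(1.26) = 0.896; severe-to-mild 0.602.
- Sham, m = 4.1: Φ(−1.08) = 0.140; Φ(0.72) = 0.764; severe-to-mild 0.624.

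| Baseline | Improved ≥1 category, EA v sham | Severe-to-mild, EA v sham |
|---|---|---|
| 21 | 0.896 v 0.764 | – |
| 29 | 0.367 v 0.189 | – |
| 30 | 0.896 v 0.764 | 0.602 v 0.624 |
| 31 | 0.855 v 0.698 | 0.626 v 0.598 |
| 32 | 0.805 v 0.626 | 0.631 v 0.556 |
| 35 | 0.603 v 0.390 | 0.541 v 0.371 |
| 42 | 0.127 v 0.046 | 0.126 v 0.046 |

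The pooled probability favours EA at every row but swings widely with baseline. It also follows a saw-tooth: it falls from 21 to 29, jumps at 30, and falls again to 42. Severe-to-mild reverses at 30 only. Averaged evenly over 30–42 it is 43.6% v 32.1% in favour of EA.

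**3. Expected counts per 68 patients as benefit grows** (baseline mean 32, SD 5):

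| Mean fall | 4.1 | 6.8 | 10 | 12 | 15 |
|---|---|---|---|---|---|
| Severe-to-mild | 19.4 | 24.5 | 25.8 | 23.6 | 17.4 |
| Any improvement | 29.1 | 41.5 | 54.2 | 59.8 | 64.9 |

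The pooled count always rises. Severe-to-mild peaks and then falls, but only beyond the planned effects. At 6.8 v 4.1 it favours EA in all five baseline distributions tried: 17.5 v 12.9 (uniform 21–42), 24.5 v 19.4 (mean 32, SD 5), 29.7 v 21.8 (mean 35, SD 4), 11.4 v 10.3 (mean 27, SD 4) and 41.7 v 37.0 (uniform 30–34).

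**4. Power by simulation.** 54 per arm, planned effects, baseline uniform 21–42, or mean 32 SD 5, or mean 35 SD 4:

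| Analysis | Power |
|---|---|
| Any improvement, chi-square | about 40–45% |
| Any improvement, logistic, baseline-adjusted | about 52–56% |
| Three-level category, proportional odds, baseline-adjusted | about 57–64% |

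Repeat runs move the chi-square and ordinal figures by up to about three percentage points; the ranking does not change. The logistic range was reproduced with baseline score and baseline category both in the model. With a single linear score term it was about 49–51%, because one straight line cannot follow the saw-tooth in step 2. In about 9–18% of simulated trials the EA arm had fewer severe-to-mild patients than sham, although EA was truly better.

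**The case against.** The strongest reply is that the heading is singular and the three shifts are every category improvement open to patients enrolled at 21 or above. The natural reading is therefore one pooled proportion, and nothing says the shifts are tested separately. This stands, and it limits the point about the severe-to-mild count to the case where the shifts are separated.

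A reader might go further than the documents allow in four ways.

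- **That a better treatment scores lower on this outcome.** The pooled proportion never reverses in these calculations. The expected severe-to-mild reversal at the planned effects needs every severe patient to start at 30.
- **That the cut-points make the outcome unsound.** A fall from 30 to 29 counts and one from 42 to 30 does not. That is true of any banded score, and the continuous primary outcome and secondary outcome 1 record the size of change.
- **That harm is hidden.** Mild-to-severe is not listed, but worsening enters both continuous LARS outcomes. Its expected number at the planned effects is about 0 to 4 per 68.
- **That this is the trial's only patient-level measure of benefit.** Distress rating, quality-of-life scales, stool diary and Wexner score are also recorded per patient.

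It can also be said that an unadjusted test remains valid under concealed randomisation, that a rank-sum test could handle ordered categories, that no power is claimed for this outcome, and that pooling rules and denominators often sit in a statistical analysis plan, which is not shown here. All fair. The missing detail alone would not be a finding. What remains is that the protocol does state an analysis family, and every test in it leaves out the strongest predictor of this outcome, which is already collected.

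**Conclusion.** The point holds as a low-cost improvement to a secondary outcome. The documents do not show a biased or reversing endpoint.

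Two things are established. The probability of improving a category depends heavily on baseline score (0.90 at 30 against 0.13 at 42 on EA), while the listed tests ignore it. And the severe-to-mild count should not be tested alone, since it is not monotone in benefit.

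Against a pooled chi-square test, baseline adjustment gains roughly 12 percentage points of power with a logistic model (40–45% to 52–56%) and 17 to 19 with an ordinal model (to 57–64%). These sizes rest on normal change with SD 5, attainable whole-number scores, and assumed baseline distributions. The direction was the same in all three distributions simulated. The primary outcome, its conclusion and the sample size of 136 are not affected.

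**What to change.** Name one endpoint for secondary outcome 2 and adjust it for baseline LARS score. Either:

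- the three-level LARS category (none, mild, severe) at each visit, compared by proportional-odds regression adjusted for baseline LARS score. This is the more powerful option and counts improvement and worsening alike; or
- improvement by at least one category among all analysed patients, compared by logistic regression adjusted for baseline LARS score. Include baseline category as a second term, because of the jump at 30.

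State that the three shifts will not be tested separately. Show the full baseline-by-visit category table by arm, including mild-to-severe, as description.

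The cost is wording in the protocol or statistical analysis plan, with no new data or visits. The small downside is a model assumption, such as proportional odds, for a secondary outcome.

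### The protocol lists no week-0 assessment for the bowel-distress NRS or the QLQ-C30, so, followed as written, neither outcome has a baseline

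*Protocol*

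**What the plan says.** Section 2.5 of the protocol (Secondary outcome) fixes the assessment times item by item:

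- Item 3, distress from intestinal symptoms: "by the Numerical Rating Scale (NRS) at Week 4, 8, 12 and 24".
- Item 4, EORTC QLQ-C30: "Patients were evaluated at weeks 4, 8, 12, and 24".
- Item 5, stool diary: "During the week 0, 4, 8, 12 and 24, we will record bowel movement frequency".
- Item 6, FIQL: "depression/self-perception, and social embarrassment at week 0, 4, 8, 12 and 24".
- Item 7, Wexner score: "we will evaluate at week 0, 4, 8, 12 and 24".
- Item 1, LARS score: "Changes in LARS Score from Baseline at Week 2, 4, 6, 12 and 24", which names the baseline outright.

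The document contains no visit table. Section 2.8 compares baseline characteristics in general terms and names neither the NRS nor the QLQ-C30. For outcomes it says: "Between-group differences in outcomes will be analyzed using t-tests, rank-sum tests, ANOVA, or χ² tests, as appropriate". It adds repeated-measures ANOVA for outcomes measured repeatedly.

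**The concern.** Five instruments share the follow-up weeks 4, 8, 12 and 24. Three of them also list week 0; the NRS and QLQ-C30 do not. A site working from this text would have no instruction to collect either one before treatment.

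Week 4 cannot stand in for a baseline, because it falls during treatment and may already contain part of the effect. Three things would be lost: the ability to report improvement from the start, the ability to see or adjust for chance imbalance on these scales, and some precision.

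The repeated-measures ANOVA would also answer a different question for these two outcomes. With week 0 in the model, the group-by-time term reflects divergence from a common start. Without it, that term reflects only divergence after week 4, and an effect established by week 4 and then stable would show only in the group main effect.

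This cannot be left to the analysis plan. Assessment times are a matter of data collection, and a baseline not taken before the first session cannot be recovered.

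**Working it through.** **1. Schedules side by side (section 2.5)**

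| Instrument | Week 0 listed | Baseline named or implied by the definition | Follow-up weeks |
|---|---|---|---|
| LARS change (item 1) | no | yes, named | 2, 4, 6, 12, 24 (week 8 is the primary outcome) |
| LARS category improvement (item 2) | no | yes, implied | 2, 4, 6, 8, 12, 24 |
| Distress NRS (item 3) | no | no | 4, 8, 12, 24 |
| QLQ-C30 (item 4) | no | no | 4, 8, 12, 24 |
| Stool diary (item 5) | yes | – | 4, 8, 12, 24 |
| FIQL (item 6) | yes | – | 4, 8, 12, 24 |
| Wexner (item 7) | yes | – | 4, 8, 12, 24 |

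Only items 3 and 4 have neither a week-0 entry nor a definition that requires a baseline.

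**2. Treatment received by the first value (section 2.4)**

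Three sessions a week in weeks 1–4 and two a week in weeks 5–8 give 3×4 + 2×4 = 20, which matches the stated total. By the end of week 4, 3×4 = 12 of 20 sessions (60%) are scheduled to have been given.

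**3. The plan's own sample size (section 2.2)**

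Inputs: difference 6.8 − 4.1 = 2.7, SD 5, two-sided α 0.05, 1:1 allocation, 20% dropout. Power is not stated; 80% is assumed.

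n per arm = 2(1.96 + 0.84)² × 5² / 2.7² ≈ 53.8, rounded up to 54. Then 54/0.8 = 67.5, rounded up to 68 per arm, or 136 in total. The stated figure is reproduced. It concerns the LARS score only, and nothing here changes it. It does give 54 completers per arm as a basis for step 5.

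**4. Variance of the group difference, relative to comparing follow-up values alone**

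Let ρ be the correlation between baseline and follow-up, with equal SDs at both times.

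- Follow-up values only: 1
- Baseline as covariate (ANCOVA): 1 − ρ²
- Change score: 2(1 − ρ)
- Standard error of follow-up-only relative to ANCOVA: 1/√(1 − ρ²)

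The protocol gives no ρ, so a range is assumed:

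| ρ (assumed) | ANCOVA | Change score | Follow-up-only SE vs ANCOVA |
|---|---|---|---|
| 0.3 | 0.91 (−9%) | 1.40 | 1/√0.91 = 1.05 |
| 0.5 | 0.75 (−25%) | 1.00 | 1/√0.75 = 1.15 |
| 0.7 | 0.51 (−49%) | 0.60 | 1/√0.51 = 1.40 |

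**5. Detectable difference at 80% power, 54 completers per arm**

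Follow-up only: (1.96 + 0.84) × √(2/54) = 0.54 SD. With ANCOVA, multiply by √(1 − ρ²): 0.51, 0.47 and 0.39 SD for ρ = 0.3, 0.5 and 0.7.

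**The case against.** **The omission may be a listing habit.** Items 1 to 4 all list post-baseline weeks only, and week 0 first appears at item 5. Item 2 omits week 0 and does not use the word baseline, yet it needs a starting LARS category, and one exists because a score of at least 21 is an entry criterion (section 2.1.3). The case report form is not shown. A reader might infer that no baseline NRS or QLQ-C30 is collected; the document shows only that none is listed. This objection stands as a limit on certainty. It does not remove the gap: item 2 cannot be computed without a baseline, whereas items 3 and 4 can, so nothing in their wording would prompt a site to collect one.

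**No stated analysis fails.** A reader might infer that the group comparison on these outcomes is biased or impossible. It is neither. Randomisation protects a comparison of follow-up values, the tests named in section 2.8 can be run on them, and neither outcome is defined as a change. This stands in full.

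**The precision gain depends on a model the protocol does not name.** Section 2.8 lists no covariate-adjusted analysis. Adding week 0 and then comparing change scores by t-test would gain nothing at ρ = 0.5 and would do worse at 0.3. A reader might therefore take the missing baseline as equivalent to discarding a quarter to a half of the participants. That holds only if ANCOVA is adopted as well and ρ is at least 0.5, and the document supports neither.

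**Related baselines exist.** LARS, FIQL, Wexner and the diary give a partial view of imbalance at the start. They do not replace a value on the same scale, least of all for general quality of life.

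**Conclusion.** The concern holds in a limited form. As written, the protocol schedules no pre-treatment NRS or QLQ-C30. If sites follow the text, change from baseline and baseline-adjusted effects cannot be estimated for these two of the nine secondary outcomes, and chance imbalance on them cannot be seen.

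The comparison of post-randomisation values remains valid. Its cost is precision: against an ANCOVA with a baseline, the standard error is about 5%, 15% or 40% larger at ρ = 0.3, 0.5 or 0.7. Those figures rest on assumed correlations, equal SDs at both times and a covariate model not currently named in section 2.8.

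The primary outcome and the total of 136 are untouched. It is a cheap improvement worth making, not a threat to the trial's main conclusion.

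**What to change.** Add week 0, before the first session, to the schedules in items 3 and 4 of section 2.5, so that they match items 5 to 7. State in section 2.8 that both outcomes are analysed with the baseline value as a covariate; plain change scores would not reliably give the precision gain.

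If a baseline is already collected in practice, the text alone needs correcting. If it was not collected for participants already treated, state that these two outcomes are compared on post-randomisation values only, and make no claim of improvement from baseline for them.

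The cost is one 30-item questionnaire and one 0–10 question at a time point already used for the FIQL, Wexner score and diary, plus a page in the case report form. No change to the sample size is needed.
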